## Abstract

**Background::**

The sequelae of Bell's palsy cause critical problem in facial appearance, as well as social and psychological problems in the patient's life. The aim of the present study is to establish clinical evidence of thread-embedding acupuncture (TEA) in the treatment of sequelae of Bell's palsy.

**Method/Design::**

This is a patient-assessor blinded, randomized, sham-controlled trial with two parallel arms. Fifty-six patients aged 19–65 years, who have experienced sequelae of Bell's palsy for >3 months, will be recruited and screened using the eligibility criteria. After screening, they will be randomly allocated to a TEA group or a sham TEA (STEA) group. Both groups will receive TEA or STEA treatment on ten predefined acupoints once a week for 8 weeks. Additionally, both groups will receive the same acupuncture treatment twice a week for 8 weeks as a concurrent treatment. Changes in the Facial Disability Index over 8 weeks will be assessed as the primary outcome. Furthermore, the House-Brackmann Grade, Facial Nerve Grading System 2.0, Sunnybrook Facial Grading System, facial stiffness score, lip mobility score, and treatment satisfaction score will be measured and analyzed as secondary outcomes. All outcomes will be assessed at baseline and at 4 and 8 weeks after screening.

**Discussion::**

The results from this trial will help establish clinical evidence regarding the efficacy and safety of TEA in the treatment of patients with sequelae of Bell's palsy.

**Trial registration number::**

KCT0002557 (Clinical Research Information Service of the Republic of Korea).

## Introduction

1

Bell's palsy, also termed idiopathic facial paralysis, is one of the most common types of peripheral facial paralysis, and the specific cause is unknown.^[1]^ Weakness of the facial muscles is the main symptom of Bell's palsy, and is accompanied by posterior auricular pain, dry eyes, hyperlacrimation, taste disorder, dry mouth, or hyperacusis.^[2]^ The severity of the symptoms varies among patients, and approximately 29% of patients are known to experience sequelae; 12% experience mild sequelae, 13% experience moderate sequelae, and 4% experience severe sequelae.^[3]^

The sequelae of Bell's palsy including synkinesis, contracture, spasm, and crocodile tear syndrome typically occur approximately 3–6 months from the onset and persist for an extended period or permanently.^[4–6]^ Patients with sequelae of Bell's palsy exhibit facial asymmetry, deformities, and abnormal movements, and complain of subjective stiffness. In a society with a high level of interest in appearance, these symptoms severely degrade patient quality of life by causing psychological or social problems.^[7,8]^

Thread-embedding acupuncture (TEA) is a novel type of acupuncture that involves the insertion and embedding of absorbable foreign substances, such as catgut or polydioxanone, into acupoints using needles. Medical thread preserves the effect of traditional acupuncture for an extended period via the mechanical and chemical stimulations of the thread.^[9,10]^ TEA has been widely used for the treatment of musculoskeletal disease,^[11,12]^ obesity,^[13]^ and cosmetic purposes, particularly for reducing facial wrinkles and improving skin elasticity.^[14,15]^

In addition to cosmetic usage, TEA has been used for therapeutic purposes for acute facial paralysis and its sequelae. Kim et al reported the adjunctive efficacy of TEA to the standard treatment of Bell's palsy within 30 days of onset.^[16]^ Ding et al reported that TEA was more effective than traditional acupuncture for the treatment of intractable facial paralysis when applied >2 months after onset.^[17]^ The clinical research of the sequelae of facial paralysis is limited to a case series,^[18]^ and the amount of evidence for TEA is not sufficient. However, because the safety and effect of TEA on facial connective tissue have been already investigated in many studies,^[19,20]^ a well-designed clinical trial will be necessary to provide further evidence and expand the therapeutic options for the sequelae of facial paralysis.

In this trial, we will compare TEA with a sham control in a rigorously designed, full-scale, randomized, controlled trial protocol to establish clinical evidence with regard to the efficacy and safety of TEA in the treatment of the sequelae of Bell's palsy.

## Methods

2

### Trial design

2.1

This clinical study is a patient-assessor blinded, randomized, sham-controlled trial with two parallel arms (1:1 ratio). The trial will take place at the Facial Palsy Center of Kyung Hee University Hospital at Gangdong. The efficacy and safety of TEA in patients with sequelae of Bell's palsy will be evaluated by comparison with sham TEA (STEA).

The protocol of this study has been approved by the Institutional Review Board (IRB) (KHNMCOH 2017-05-001). The trial has also been registered at the Clinical Research Information Service of the Republic of Korea (Registration Number: KCT0002557). All research procedures comply with Korean Good Clinical Practice (KGCP) and the Declaration of Helsinki. The methodological details of TEA were established in accordance with the revised Standards for Reporting Interventions in Clinical Trials of Acupuncture (STRICTA).^[21]^ The items of protocol refer to the Standard Protocol Items: Recommendations for Interventional Trials (SPIRIT).^[22]^

### Participants

2.2

Individuals of both sexes fulfilling the following inclusion criteria will be included in this study:

(1)age 18–65 years(2)a diagnosis of Bell's palsy made ≥3 months prior to screening(3)Facial Disability Index (FDI) <80 on the social aspect and <70 on the physical aspect(4)ability to communicate adequately with the researcher and respond to the questionnaire in writing(5)willingness to sign a form stating that they will not receive any treatment other than the prescribed treatment within the treatment period, and(6)willingness to participate in the study after providing written informed consent.

Participants with the following characteristics will be excluded:

(1)a history of receiving any other treatment that may affect the study outcomes for 2 months prior to the screening (oral administration of steroids or antiviral drugs, surgical history for treatment of facial palsy such as facial nerve compression, or facial TEA);(2)history of hypersensitivity to TEA or severe keloid;(3)Ramsay-Hunt syndrome;(4)bilateral facial nerve palsy or recurrent facial nerve palsy (more than two occurrences);(5)secondary facial nerve palsy from multiple neuritis, tumor invading the temporal bone, trauma, brain contusion, or stroke;(6)chronic otitis media, temporomandibular fracture, or history of ear surgery;(7)inappropriate condition for TEA administration due to skin disease or hemostatic disorder (prothrombin time international normalized ratio [PT INR] >2.0 or taking anticoagulant);(8)liver function abnormality (aspartate transaminase [AST] or alanine transaminase [ALT] levels greater than twofold the normal level);(9)renal function abnormality (serum creatinine or blood urea nitrogen [BUN] levels greater than twofold the normal level);(10)pregnancy or breastfeeding;(11)mental illness resulting in inability to comply with the clinical trial protocol; or(12)any other condition rendering the individual unsuitable for inclusion in the trial, as determined by the principle investigator (PI).

### Procedure

2.3

Fifty-six patients with sequelae of Bell's palsy will be recruited at Kyung Hee University Hospital at Gangdong. They will be provided with detailed information regarding the study, and only those who participate voluntarily will be included in the study. Those who agree to participate and sign the informed consent form will be screened for eligibility. If they meet the eligibility criteria, the participants will be randomly allocated to the TEA group or the STEA group. After random allocation, 16 visit sessions for treatment and assessment will be conducted according to an 8-week appointed schedule (Fig. 1).

**Figure 1 F1:**
[figure not shown]
Standard Protocol Items: Recommendations for Interventional Trials (SPIRIT) figure.

During the trial period, participants who meet the following criteria will be excluded from the study:

(1)taking medication or receiving additional treatment that is expected to affect the outcome of the study for the purpose of treating the sequelae of Bell's palsy,(2)withdrawal of consent for study participation because the participant does not wish to continue,(3)missing more than 5 of 16 visit sessions,(4)occurrence of a serious adverse event (AE),(5)critical protocol violation such as violation of eligibility criteria,(6)decision of the PI that the participant should be removed from the trial.

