### Statistical methods

2.10

The data will be corrected using the “last observation carried forward” method and then analyzed using the “intention-to-treat” analysis. The independent t-test or the Mann-Whitney U test for continuous variables and the Chi-square test or Fisher's exact test for categorical variables will be used to compare differences in general characteristics between the groups. As a primary outcome, changes in the FDI from baseline to the end of the 8-week treatment will be compared between the groups using the independent t-test. As secondary outcomes, changes in HB Grade, FNGE 2.0, SFGS, facial stiffness score, lip mobility score, and treatment satisfaction score will be also analyzed in the same way. All statistical analyses will be performed using PASW statistics 18, and the statistical significance level will be set at 0.05 (two-sided).

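### Participants who meet a removal criterion leave the study, not only the treatment, so the intention-to-treat analysis leans on carried-forward FDI values that could have been observed

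*Protocol article*

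**What the plan says.** Section 2.3 (Procedure) places the visits after allocation: "After random allocation, 16 visit sessions for treatment and assessment will be conducted according to an 8-week appointed schedule". The list that follows Figure 1 opens with "During the trial period, participants who meet the following criteria will be excluded from the study" and gives six criteria:

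1. "taking medication or receiving additional treatment that is expected to affect the outcome of the study"
2. withdrawal of consent
3. "missing more than 5 of 16 visit sessions"
4. a serious adverse event
5. "critical protocol violation such as violation of eligibility criteria"
6. "decision of the PI that the participant should be removed from the trial"

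The opening line and the sixth criterion both speak of leaving the study or trial, not of stopping study treatment.

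Section 2.6.1.1 has the FDI measured at screening and at weeks 0, 4 and 8, with week 8 as the primary endpoint. Section 2.10 (Statistical methods) says that the data are first completed by LOCF and "then analyzed using the “intention-to-treat” analysis". Section 2.12 (Safety) schedules laboratory tests at pre-screening and at week 8, and has the course of every adverse event recorded. Section 2.7 allows for 10% dropout. Sections 2.3 and 2.10 do not refer to each other.

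**The concern.** An intention-to-treat comparison is protected by randomisation to the extent that outcomes are obtained from everyone randomised. Here the protocol itself takes people out for what happens to them during the trial. Someone who does poorly may seek other treatment or stop attending, and someone who reacts badly to the procedure may have a serious adverse event. Such events can differ between arms. The sixth criterion is open-ended.

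Most of these people could still complete a ten-item questionnaire at week 8. If they are out of the study, that value is not assured, and neither is the routine week-8 laboratory panel. What is at stake is avoidable, possibly arm-related loss of the primary outcome, with replacement values produced by the removal rule. An analysis plan can define analysis sets, but it cannot recover values that were never collected.

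**Working it through.** **Inputs from the article.** Section 2.7: σ = 23.30, d = 21.54, 90% power, 10% dropout, 28 per group. Section 2.10: two-sided 0.05. Section 2.6.1.1: FDI at weeks 0, 4 and 8. Removal rates, overall or by arm, are not given and are assumed below.

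**The plan's own figure.** n = 2 × [23.30 × (1.960 + 1.282) / 21.54]² = 24.59, so 25 per group. Then 25 / 0.90 = 27.8, so 28. The stated size reproduces and is not in dispute.

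**What LOCF can carry.** Only two values can stand in for week 8:
- removal before week 4: the week-0 value, so the change from baseline is exactly 0;
- removal between weeks 4 and 8: the week-4 value.

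**Illustration A, unequal removal.** Assume that both arms truly improve by 20 points, that 15% of one arm and 5% of the other are removed before week 4 (about 4 and 1 of 28), and that those removed would have improved like the rest.
- Arm with 15% removed: 0.85 × 20 + 0.15 × 0 = 17
- Arm with 5% removed: 0.95 × 20 + 0.05 × 0 = 19
- False difference: 19 − 17 = 2 points, against the arm with more removals

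The standard error is 23.30 × √(2/28) = 6.23, so 2 points is 0.32 standard errors. With the SD unchanged, two-sided type I error is about P(Z > 1.960 − 0.321) + P(Z < −1.960 − 0.321) = 0.051 + 0.011, or about 6% instead of 5%. If removal came after week 4 and half of the improvement had been reached by then (also assumed), the false difference would be 0.10 × 10 = 1 point.

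**Illustration B, equal removal.** Assume that a fraction f of each arm is removed before week 4 and that the SD is unchanged. The expected difference becomes (1 − f) × 21.54. Power at 28 per group is Φ(difference / 6.23 − 1.960).

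| f | Expected difference | Power (normal approximation) | Power (t-test) |
|---|---|---|---|
| 0 | 21.54 | 93.3% | 92.5% |
| 10% | 19.39 | 87.6% | 86.4% |
| 20% | 17.23 | 79.0% | 77.6% |
| 30% | 15.08 | 67.8% | 66.2% |

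Removal that is balanced between arms therefore still costs power. If all of the planned 10% were lost before week 4, power would fall slightly below the 90% target.

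**The case against.** The case on the other side has several parts.

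- **Removed participants are not said to leave the analysis.** This stands. A reader might infer from Section 2.3 that they are dropped and that intention to treat is defeated. The order in Section 2.10, LOCF first and intention to treat second, makes sense only if people without a week-8 value stay in their allocated arm.
- **Not every criterion is a post-randomisation event.** This stands. The only example under the fifth criterion is an eligibility violation, which predates allocation even if found later. Withdrawal of consent is a legitimate end of participation.
- **Safety follow-up is not cut off.** This largely stands. A reader might infer that data stop after a serious adverse event, but Section 2.12 has the progress of all adverse events recorded. Only the routine week-8 panel is not assured.
- **Blinding limits arm-related removal.** This stands in part. Section 2.9 blinds patients and assessors. Practitioners know the allocation, and a true difference in effect or tolerability can drive removal without unblinding.
- **The article is condensed, and follow-up after removal may be set out in the full protocol.** This is why the loss is described as not assured rather than certain. But the point rests on a rule that the article states, not on a missing detail.
- **The magnitude is modest and rests on assumed rates.** This stands. Two points is 2 / 21.54 = 9% of the planned difference. It also supposes that every loss is carried from baseline. Part of the planned 10% would be consent withdrawal or ordinary non-attendance, which no rewording recovers.

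A reader might also object that the visit rule counts acupuncture-only visits together with study-intervention visits. The article does not present that rule as a measure of exposure to the study intervention, and this point does not depend on it.

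**Conclusion.** The point holds in a limited form. Section 2.3 ends participation in the study, not only treatment, for events that mostly follow randomisation and may relate to arm or response. As written, week-8 FDI and the routine week-8 laboratory tests are not assured for these people, so the analysis in Section 2.10 rests on week-0 or week-4 values for them. That undermines the intention-to-treat analysis without defeating it.

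The likely size is small to moderate: about 2 FDI points of bias under the assumed 15% against 5% early removal, less with later removal, and some loss of power even when removal is balanced. These figures are illustrations under stated assumptions, not estimates. This is an inexpensive improvement worth making before the data are lost. It does not invalidate the design.

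**What to change.** Reconcile Sections 2.3 and 2.10 by a short amendment that:

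- states that meeting one of the listed criteria does not by itself end outcome assessment;
- unless consent to follow-up is withdrawn, seeks FDI at weeks 4 and 8 and the planned week-8 safety tests from every randomised participant;
- states that all randomised participants are analysed in the arm to which they were allocated, so that LOCF is needed only where a value truly could not be obtained.

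The criteria themselves, and any decision on when treatment stops, are left as they are. A change to how visits are counted or a per-protocol set is not needed for this.

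The cost is the amendment and a few extra assessment visits for participants who would otherwise have left. It does not help with participants who withdraw consent to follow-up or cannot be reached; their values remain missing.

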### Interventions

2.4

In both groups, TEA or STEA will be administered once a week for 8 weeks using a 29 G, 40-mm TEA needle (Hyundae Meditech, Wonju, South Korea) on 10 predefined acupoints selected by an expert group of Korean medical doctors according to STRICTA (Table 1). The selection of acupoints and details of the procedure have been determined by a consensus of clinical experts and modified from those used in previous studies.^[18,23]^ All therapeutic procedures will be performed by qualified acupuncture specialists.

**Table 1 T1:**
[figure not shown]
Details of the thread-embedding acupuncture treatment using the STRICTA 2010 checklist.

After covering the patient's eyes and sterilizing the skin, practitioners will conduct the intervention procedure. TEA will be transversely inserted 4 cm from one acupoint toward another acupoint in the layer termed the superficial musculoaponeurotic system,^[24]^ and only the needle will be removed while leaving the thread in the face. For the sham control comparison, thread-removed needles will be used in the STEA group instead of normal TEA in the TEA group. The thread removal procedure will be performed aseptically and discreetly for prevention of infection and patient-blinding. The practitioners will minimize the conversation during the interventions, aside from that essential to the procedure, in order to prevent bias.

### Concurrent treatment

2.5

As a concurrent treatment, both groups will receive the same traditional needle acupuncture treatment twice a week for 8 weeks. One of the two acupuncture treatments will be planned on the same day as the intervention. Hence, acupuncture treatment will be performed immediately after TEA or STEA. For the acupuncture treatment, a 0.20 × 30 mm disposable acupuncture needle (Dongbang Medical, Seongnam, Korea) will be inserted at a depth of 5 mm and will be retained for 30 min on the following 28 acupoints: GV26, CV24, and both sides of ST3, ST4, ST6, ST7, LI20, BL2, GB14, TE23, GB1, TE17, LI4, and LR3.

Other than acupuncture treatment, any treatment that may affect the results will be prohibited. Medications that the participants have been taking from 4 weeks before the trial will be allowed at the discretion of the investigators depending on whether they affect the symptoms. All information regarding medications administered to the participants should be recorded in the case report form (CRF).

### Outcomes

2.6

The primary outcome is a change in the FDI score. The secondary outcomes will be the House-Brackmann Grade (HB Grade), Facial Nerve Grading System 2.0 (FNGS 2.0), Sunnybrook Facial Grading System (SFGS), facial stiffness score, lip mobility score, and treatment satisfaction score. Additionally, all AEs will be recorded at each visit. All assessments will be performed by independent researchers who are not involved in the scheduled intervention.

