### Safety

2.12

To monitor the safety of the intervention and prepare for the occurrence of AEs, the following laboratory tests will be carried out at the pre-screening point and at week 8 when the all treatment is completed: complete blood count (white blood cells, red blood cells, hemoglobin, hematocrit, and platelets), liver function test (AST, ALT, alkaline phosphatase, and total bilirubin), renal function test (BUN and creatinine), erythrocyte sedimentation rate, and C-reactive protein. PT INR will be carried out if participants have hemostatic disorders or take anticoagulants. For women of childbearing age, the possibility of pregnancy should be excluded by a urine human chorionic gonadotropin test using a stick-type pregnancy test, and education of the need for medically acceptable contraception during the study period should be provided.

At each visit, the researchers will measure blood pressure, pulse rate, and body temperature, and assess the occurrence of AEs and changes in the medications being taken. Information regarding expected AEs, as well as a contact number, will be provided to the participants along with the informed consent form before the pre-trial screening. If AEs do occur, the PI will evaluate the severity of the incident, as well as its relation to the interventions, and provide proper examination and treatment in accordance with the compensation rules. The progress of all AEs will be recorded in the CRF and managed in accordance with the standard operation protocol of the IRB and the regulation of KGCP.

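### Scheduled adverse event enquiry ends with the 8-week treatment schedule, so the last thread session has 0 to 7 days of active observation and later thread-related events are not systematically captured

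*Protocol article*

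**What the plan says.** All references are to the protocol article.

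- **AE collection.** Section 2.6 states that "all AEs will be recorded at each visit". Section 2.12 repeats this: at each visit the researchers "assess the occurrence of AEs and changes in the medications being taken".
- **Visits.** Section 2.3 states that "16 visit sessions for treatment and assessment will be conducted according to an 8-week appointed schedule". The text mentions no later visit or call.
- **Thread sessions.** Section 2.4 states that "TEA or STEA will be administered once a week for 8 weeks". Section 2.5 puts each session on one of the two weekly acupuncture days, without saying which.
- **What remains in the tissue.** Section 2.4, after Table 1, states that in the TEA arm "only the needle will be removed while leaving the thread in the face". The sham arm uses the same needle with the thread taken out.
- **Last safety laboratory tests.** Under section 2.12 these are done "at the pre-screening point and at week 8 when the all treatment is completed".
- **Other provisions.** Section 2.12 gives participants a contact number and has the course of AEs recorded in the case report form.
- **Aim.** The Abstract expects the results to help "establish clinical evidence regarding the efficacy and safety of TEA", and does not limit safety to the treatment period.

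**The concern.** The arms are designed to differ in one thing, the thread, and the thread stays behind when the needle is withdrawn. Section 1 says of it: "Medical thread preserves the effect of traditional acupuncture for an extended period". That sentence is about therapeutic effect, but it shows that the authors regard the thread as active beyond the session.

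Active enquiry about harm nevertheless stops at the end of treatment. The first session is followed for seven or eight weeks and the last for a week at most. An event caused by needling can occur in either arm and will mostly show while visits continue. A delayed event caused by the thread can occur only in the TEA arm, and it is the kind that falls outside the window. What is at stake is the completeness of the safety evidence that the article says it will provide.

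**Working it through.** **Inputs.** Eight weekly thread or sham sessions (2.4); 16 visits in 8 weeks, so two per week (2.3); AE enquiry at visits (2.6, 2.12); the session's place within the week is not fixed (2.5). The article states no observation time per session, so there is no figure on this point to reproduce.

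**Step 1: active observation per session.** Time from session *k* to the last scheduled enquiry, under the placements that the text allows:

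| Placement | Days for sessions 1 to 8 | Mean |
|---|---|---|
| Session on the second weekly visit, so session 8 is on visit 16 | 49, 42, 35, 28, 21, 14, 7, 0 | 24.5 days (3.5 weeks) |
| Session on the first weekly visit, visit 16 closes the trial | 52.5, 45.5, 38.5, 31.5, 24.5, 17.5, 10.5, 3.5 | 28.0 days (4.0 weeks) |
| Session on the first weekly visit, closing assessment on day 56 | 56, 49, 42, 35, 28, 21, 14, 7 | 31.5 days (4.5 weeks) |

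Session 8 thus gets 0 to 7 days. In the longest case five of the eight sessions reach 28 days and none exceeds 56. Sessions with a week or less number two of eight in the shortest case and one of eight in the longest.

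**Step 2: illustration of what the window captures.** The article gives no latency, so the following is an assumption: time from insertion to a delayed event is exponential with median *m* weeks, and each session is equally likely to cause one. The captured share is the mean over sessions of 1 − 2^(−t/m), with *t* in weeks. The shortest case has t = 7, 6, ..., 0 and the longest has t = 8, 7, ..., 1. A contact four weeks later adds 4 to each *t*.

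Worked example, m = 4: the sum of 2^(−t/4) over t = 0 to 7 is 4.71, so the captured share is 1 − 4.71/8 = 0.41. Over t = 1 to 8 the sum is 3.96, which gives 1 − 3.96/8 = 0.50.

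| Assumed median latency | Plan as written | One contact four weeks later |
|---|---|---|
| 2 weeks | 60-72% | 90-93% |
| 4 weeks | 41-50% | 71-75% |
| 8 weeks | 25-31% | 47-51% |

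These are shares of delayed events, given that such events occur. They say nothing about how many there are.

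**Step 3: effect on the rest of the design.** The sample size in 2.7 reproduces: 2 × (23.30 × (1.960 + 1.282)/21.54)² = 24.59, rounded up to 25, and 25/0.9 = 27.8, so 28 per group. Neither this nor the week-8 comparison of the Facial Disability Index depends on the AE window.

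**The case against.** **The article condenses a fuller protocol.** The SPIRIT schedule and the STRICTA table are not visible here, and section 2.12 refers AE management to the ethics board's procedures and Korean good clinical practice. A post-treatment contact could be written there. This stands as a caution. However, the article itself fixes the number of visits, their span and the final laboratory date, and every assessment it names ends at week 8. That is a stated horizon, not merely an omitted detail.

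**The authors regard the thread as low risk.** Section 3 describes polydioxanone as safe with low tissue reactivity, and section 1 says that facial safety has been studied before. This may explain a short follow-up. It does not remove the need to observe the last sessions in a trial that reports on safety.

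**The sample is small.** Even with complete follow-up and no event among 28 TEA patients, the one-sided 95% upper limit for the event rate would be 1 − 0.05^(1/28) = 10.1%. A later call improves ascertainment, not precision. This stands.

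**A stronger reading is tempting.** A reader might infer that late events are lost altogether and that the comparison between arms is biased towards no difference. The documents do not support that. The contact number leaves a passive route for late reports. Participants are blinded (2.9), so there is no shown reason why spontaneous reporting should differ between the arms. Section 2.10 describes no formal test of AEs between arms that could be distorted. Nor should the lower ends of the ranges above be read as the estimate: they assume that session 8 falls on the very last visit, and the latencies come from no document.

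**Conclusion.** The point holds in a limited form. As written, active AE enquiry gives the last thread session 0 to 7 days and the eight sessions a mean of 3.5 to 4.5 weeks; this follows from the stated schedule without further assumption. Thread-related events after that are not systematically captured, and they concern the TEA arm alone. The capture percentages are conditional on an assumed exponential latency and serve only to show that one later contact could matter. It is a modest but worthwhile improvement to the safety evidence, with no bearing on the primary endpoint or the number of patients.

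**What to change.** In sections 2.6 and 2.12, add one AE telephone enquiry after the last session, in both arms, with a fixed script, made by existing staff not told the allocation. State that the AE period runs to that contact. The sponsor should choose the interval and justify it from the absorption time of the thread used; the four weeks in the illustration are not a recommendation. The call need cover AEs only.

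If the call is not added, limit the safety conclusion to events during the 8-week treatment period and say so in the article's aim.

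Cost of the call: a protocol and ethics amendment, about 56 short calls (28 per group × 2), a slightly longer follow-up and a few non-responders. The alternative is a change of wording only.
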